**FIGURE 2 F2:**
[figure not shown]
Virtual hospital scenario in Gait Real time Analysis Interactive Lab (GRAIL).

The second scenario presents a virtual city scenario that portrays an urban environment with a pedestrian zone in which bicycles and pedestrians interact in virtual space. Direction and number of bicycles and pedestrians crossing or passing the participant will be varied, thus providing a dynamic and realistic representation of urban life in virtual space. The scenario includes a predefined sequence of 11 scripted events, which are distributed at regular intervals of approximately 30 meters along the walking path. These events consist of various interaction types, including pedestrians stepping out of buildings and crossing or walking alongside the participant’s path, passing maneuvers, stationary individuals initiating movement as the participant approaches, irregular or nonlinear walking patterns and bicycle crossings. After about 215 meters, the environment transitions to a section featuring architectural arches. Participants continue walking under the arches while additional event types occur.

##### Electroencephalography (EEG)

2.8.1.2

Brain activity will be captured during walking utilizing a mobile EEG system (LiveAmp, Brain Products GmbH, Gilchingen, Germany) equipped with 64 gel-based active Ag/AgCl electrodes (actiCAP slim electrodes, Brain Products GmbH, Gilchingen, Germany) positioned according to the modified 10-10 system (Nuwer et al., 1998). The following electrode positions will be used: Fp1, Fp2, AF7, AF3, AFz, AF4, AF8, F7, F5, F3, F1, Fz, F2, F4, F6, F8, FT9, FT7, FC5, FC3, FC1, FCz, FC2, FC4, FC6, FT8, FT10, T7, C5, C3, C1, Cz, C2, C4, C6, T8, TP9, TP7, CP5, CP3, CP1, CPz, CP2, CP4, CP6, TP8, TP10, P7, P5, P3, P1, Pz, P2, P4, P6, P8, PO7, PO3, POz, PO4, PO8, O1, Oz, O2. Electrode FPz will be used as a ground electrode. Impedances will be kept below 25 kOhm, which has been shown to be eligible for active electrodes (Laszlo et al., 2014). EEG signals will be acquired with a sampling rate of 500 Hz. Data will be recorded during the walking tasks on day 2 (cf. Participant timeline). For each walking trial, a separate EEG recording will be made. Both amplifiers of EEG and fNIRS will be carried within a vest worn by the participant. Efficient cable management ensures full freedom of movement for the upper and lower extremities as well as for the head. Synchronized timestamps for the beginning and end of the trials as well as for the approaching doors will be send via LSL (cf. System integration – fNIRS, EEG and GRAIL). Timestamps for FOG episodes will be extracted from the video data and subsequently incorporated into the EEG data (cf. FOG detection).

##### Functional near-infrared spectroscopy (fNIRS)

2.8.1.3

Hemodynamic activation during walking will be recorded using two 8 x 8 mobile NIRSports 2.0 systems (NIRx Medical Technologies, Glen Head, NY, USA) and Aurora recording Software (NIRx Medical Technologies, Glen Head, NY, USA). The two systems will be configured in a single-subject tandem setup, including 32 dual-tip optodes. The setup consists of 16 light emitters and 15 long-distance detectors spaced approximately 3–4 cm apart (long channels), adapted to the 10-05 system standards (Oostenveld and Praamstra, 2001). Additionally, eight short channels detectors will be utilized with a source-detector distance of about 1 cm. This distance allows for assessment of extracerebral physiological and mechanical artifacts, while not capturing brain-related hemodynamic activity (Yücel et al., 2015). The sensor arrangement will create 46 long-distance channels focusing on several key areas of interest (Cockx et al., 2024), spanning frontal, central, parietal, and occipital regions across both hemispheres (cf. Figure 3). For different head circumferences, four different cap sizes (Bach, 1996; Borg, 1982; Koopman et al., 2019), 60 cm; NIRScap, EASYCAP GmbH, Herrsching, Germany) will be used to ensure a comfortable fit and to consider the anatomical differences in the brain. The sources emit infrared light pulses at two wavelengths (760 nm and 850 nm) with a modulation frequency of 5.086 Hz (continuous wave fNIRS). Further, sources are time-multiplexed to prevent crosstalk between channels. All optodes are shielded from external light sources (e.g., screen light) by an opaque cover. To ensure that participants have sufficient freedom of movement, all optode cables and the amplifier are firmly stowed and held in a small backpack on the participants’ backs. Further experimental and statistical measures will be implemented, including a high number of FOG trials (up to 15 FOG trials per person) and advanced statistical approaches (multilevel models) to improve the robustness of our findings (Ayaz et al., 2022; Yücel et al., 2021).

**FIGURE 3 F3:**
[figure not shown]
Probe setup. Bi-hemispheric setup covering whole head with 64 EEG electrodes (white) and with 16 sources (red), 15 long-distance detectors (blue), and 8 short channel detectors (blue circle outlines); Graphics were created with NIRSite from NIRx Medical Technologies (courtesy of NIRx Medical Technologies LLC; https://nirx.net).

##### Kinematics and kinetics

2.8.1.4

Kinematic and kinetic data will be captured using VICON Nexus 2.12 (VICON; Oxford, United Kingdom) software, two independent ground reaction force plates, fixed 10 infrared cameras (VICON VERO; VICON Motion Systems Ltd; Oxford, United Kingdom), and reflective markers. The cameras will be calibrated before each recording session and capture videos at a frequency of 100 Hz. Reflective markers will be positioned according to the Plug-in-Gait full body marker set, with a total of 39 markers for each participant (Vicon, 2023). The following angles will be calculated: elbow angles, head angles, neck angles, shoulder angles, spine angles, thorax angles, wrist angles, ankle angles, hip angles, knee angles, and the pelvis angles. The joint angles will be calculated by the VICON Nexus 2.12. software using previously collected body measurements (VICON; Oxford, United Kingdom). The full-body joint angles provide information about the movement of the whole body, including head and trunk movement, that is used for signal-quality control and artifact handling of the EEG and fNIRS data. They are not treated as outcome measures (cf. Outcomes). The measuring system utilizes the two independent force plates to record 3D ground reaction forces at a frequency of 1000 Hz for each leg separately (Motek Medical; the Netherlands). The VICON Nexus software will export ground reaction force data, raw marker trajectories and joint angles. The raw marker trajectories will be exported as XYZ coordinates. The joint angles will be exported as either vector, relative, or absolute angles, depending on the joint. The force data will be exported for each force plate individually, including location and force vector, as well as a combined value.

##### FOG detection

2.8.1.5

Participants will be recorded by three cameras (Basler ace acA720-290gm, Basler AG) operating at 50 fps. Two cameras are positioned laterally to capture movements in the sagittal plane, and one is positioned behind the participant to record movements in the frontal plane. Two independent experts will assess these videos for FOG episodes and annotate detected episodes using the video annotation tool ELAN, following the updated guidelines of Gilat et al. (2026) (The Language Archive, 2024). This procedure represents the gold standard in the field for detecting and classifying FOG (Moore et al., 2013). Additionally, each annotated episode will be classified by the motor context at its onset as either walking-FOG (forward locomotion, including doorway passage and straight walking) or turning-FOG (360° turning). This classification is based on the video and the synchronized task markers. The percentage of time spent frozen will be calculated by dividing the duration of the episodes annotated as FOG by the duration of the gait tasks.

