## Introduction

1

James Parkinson’s “An Essay on the Shaking Palsy” (1817) introduced the first formal medical description of Parkinson’s disease (PD), which today is one of the most common neurodegenerative disease worldwide. During recent decades, PD has been on the rise, with nearly 1 million people being affected by PD in the US alone, and this number is expected to rise to 1.2 million by 2030 (Marras et al., 2018). People with PD suffer from a wide range of motor symptoms, including tremors, muscle rigidity, bradykinesia, and postural instability (Giladi et al., 2001; Nutt et al., 2011). One of the most debilitating motor symptoms of the disease, however, is freezing of gait (FOG), of which approximately 60% of people with PD are suffering during the course of their disease (Macht et al., 2007; Zhang et al., 2021). FOG is described as a sudden and temporary inability to move forward. FOG manifests as either small steps in a forward shuffling motion, alternating trembling of the legs on site with a frequency of about 3–8 Hz, or akinesia (Hausdorff et al., 2003; Moore et al., 2008; Schaafsma et al., 2003). Typical triggers for FOG can be categorized as movement-related, cognition-related or emotion-related. Movement-related triggers of FOG include turnings, passing through (narrow) doorways or passages, and gait initiation (Cockx et al., 2023; Palmisano et al., 2022; Spildooren et al., 2019). Cognition and emotion-related FOG triggers, in turn, typically refer to situations with increased cognitive load or higher levels of anxiety (Martens et al., 2016; Pimenta et al., 2019; Spildooren et al., 2010). Unfortunately, the underlying neural mechanisms and pathways of FOG remain largely unclear, and current treatment options, such as dopaminergic medication and deep brain stimulation, often remain ineffective, particularly in resolving FOG. Given these challenges, so-called cueing strategies have emerged as effective alternatives to reduce FOG during daily life activities, among which vibrotactile cueing seems to be particularly promising. In this study, we will explore the neurophysiological correlates of FOG and assess the efficacy of vibrotactile cueing as a potential intervention to alleviate this debilitating symptom.

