On the second day, the session will start with participants being prepared for motion capture by applying reflective markers to the whole body and putting on a safety harness, followed by a short re-familiarization with the treadmill’s self-paced mode. Once comfortable, preparations for neurophysiological measurements will proceed. Participants will be seated and a cap, already equipped with 64 EEG electrodes, will be aligned on their head using anatomical landmarks (nasion, inion and preauricular points). Electrodes will be prepared with gel, followed by preparation of all optodes until adequate signal quality for both EEG and fNIRS is achieved (cf. sections Electroencephalography (EEG) and Functional near-infrared spectroscopy (fNIRS) for detailed information). The experimental procedure will begin with a detailed instruction of the virtual walking task and testing procedure. Participants are then performing a maximum of four walking trials, each lasting roughly 10 min. Before every trial, participants are asked to stand still for 1 min, which will serve as a baseline period for neurophysiological analyses. After each trial, a short break will be administered. If the total number of FOG episodes is below 15 and the patient is reporting a moderate amount of exertion, the next trial will be initiated. Exertion will be assessed using objective measures, including the Rate of Perceived Exhaustion Scale (Borg, 1982) and the Rating Scale Mental Effort (Zijlstra and Van Doorn, 1985). Participants will perform two blocks, each consisting of four walking trials. A break of 10 to 30 min will be provided between both blocks. Cueing and no-cueing will be administered in alternation. After 15 FOG events, the experiment will be stopped after completion of the current trial. The rationale for this design choice is to collect a sufficient number of FOG episodes, while not over exhausting participants. After the walking task 2, further questionnaires regarding the usability and feasibility of the prototype will be handed to the participants (cf. Screenings). For an overview of the whole procedure, see Figure 1. The neurophysiological preparations and measurements will be undertaken by the same personnel described above, who are trained in the preparation and application of various neuroimaging methods.

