Virtual scenarios will be created with D-Flow (Motekforce Link, Amsterdam, the Netherlands). The virtual scenarios depict a hospital-like environment (see Figure 2) with an endless corridor with wooden flooring (brownish color) and a city scenario in a pedestrian zone. In the hospital scenario, which will be described here as an example, participants walk through a hospital-like corridor that contains visual representations of doors to other rooms (patient bedroom, dinner, medical specialists) to the right and left of the corridor in a well-lit environment. In addition, the scenario includes other smaller decorative objects (e.g., flower pots, benches, poster boards, lighting and ventilation, or trolleys) and occasional intersections with further decorative enrichments. These details aim at providing a more realistic and immersive virtual environment. The main aspect of the virtual hospital scenario are opaque automatic doorways. These doorways are used to mimic typical narrow doorways/passages in the real world that often cause FOG in PD (Cockx et al., 2023). The doors are designed as sliding doors with a motion sensor placed directly above the door. Behind some doors, objects such as a bench, potted flower, or trolley moving laterally toward the participant are presented randomly to introduce unpredictable events during the scenario. The automatic doors open bidirectionally at a speed of 0.3 m/s. They begin to open when the participant is positioned between 3.1–4 m (pseudorandomized, in steps of 0.1 m) in front of them. The doors open to a width ranging from 74 and 100 cm (pseudorandomized, in steps of 1 cm). The scenario contains 10 doors, each separated by approximately 30 m. A rotation symbol is projected onto the floor 8.5 m behind each door. The symbol consisted of two arrows pointing in the same direction and forming a circle, indicating that participants had to perform a 360° rotation. Once participants reached the floor-projected rotation cue and came to a stop, an enlarged version of the same cue was additionally displayed in the center of the screen. The required turn direction followed a fixed alternating sequence across the ten doors, always starting with a right turn at the first door, resulting in five right turns and five left turns.

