#### Statistical methods

2.8.4

To address our main research objectives, we will employ linear mixed effects models for our analyses. These models are well-suited for handling repeated measures and allow us to take advantage of the multi-trial data structure, while also accounting for both within-subject and between-subject variability. FOG episodes will be analyzed separately by motor context, distinguishing walking-FOG (forward locomotion, including doorway passage and straight walking) from turning-FOG (360° turning). Each FOG type will be compared against its corresponding unimpaired movement (Handojoseno et al., 2015a). The number of FOG episodes per type and participant will be reported.

First, we will identify cortical brain regions showing differential activation prior to the kinematic onset of FOG. Dependent variables include spatiotemporal characteristics of electrocortical and also hemodynamic brain activity that will be compared between FOG episodes and the corresponding period of unimpaired walking or turning. Second, we aim to delineate the neural signatures of FOG episodes, focusing on the temporal and frequency dynamics within the cortical areas of interest as defined by the first part of our analysis. This step includes analyzing the coherence of the neural dynamics across the brain regions involved. Lastly, we will examine if and how vibrotactile cueing may alter the neural signatures of FOG described above and whether it contributes to improved gait behavior when walking through virtual environments. This analysis will also focus on the reduction of the percentage time frozen, changes in kinematic and kinetic aspects of gait. All analyses will include relevant covariates, such as disease stage, motor symptom severity, prior experience with cueing and random effects accounting for inter-subject variability, and to investigate interindividual differences. To address the large number of comparisons across modalities, all analyses will include appropriate correction for multiple comparisons to control the rate of false-positive findings, using established methods such as Bonferroni correction or cluster-based permutation testing (Maris and Oostenveld, 2007).

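### Freezes at gait initiation have no class and no matched comparator: the two-way walking/turning rule lets standing or turning enter the pre-FOG window as if it were a FOG signature

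*Protocol article*

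**What the plan says.** Section 2.8.1.5 (FOG detection) gives a rule for all annotated episodes: the class depends on the motor context at onset and is "either walking-FOG (forward locomotion, including doorway passage and straight walking) or turning-FOG (360° turning"). There is no class for gait initiation and none for other episodes.

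Section 2.8.4 (Statistical methods) repeats the two types and sets a like-for-like principle: "Each FOG type will be compared against its corresponding unimpaired movement". The comparison periods it names are unimpaired walking and unimpaired turning. It also promises episode counts per type and participant.

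The Introduction treats initiation as a separate trigger: "Movement-related triggers of FOG include turnings, passing through (narrow) doorways or passages, and gait initiation".

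The tasks produce starts:

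- Section 2.5 (Participant timeline): "Before every trial, participants are asked to stand still for 1 min". That minute also serves as the neurophysiological baseline.
- Section 2.8.1.1 (Virtual walking scenarios), hospital scenario: "The scenario contains 10 doors, each separated by approximately 30 m", and "A rotation symbol is projected onto the floor 8.5 m behind each door". Participants come to a standstill at the symbol and make a full turn, five to the right and five to the left.

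Section 2.8.2.1 (EEG) takes the 5 s before the FOG marker and describes that window as the passage from regular locomotion into FOG.

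**The concern.** A start hesitation begins when the person is neither walking forward nor turning through 360°, so it meets neither definition. The rule still has to place it in one of the two. Its comparator is then walking or turning, never an unimpaired start.

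This matters because the primary outcomes for RO1 and RO2 are EEG changes in the window before onset. If that window holds standing, or the end of a turn, on the FOG side and steady walking on the comparator side, the contrast mixes two differences: freezing against not freezing, and one motor state against another. A mixed model with random subject effects does not separate them, because motor state would differ systematically between the two sides for these episodes. RO3 then asks whether the signature found in this way is weaker before doorways under cueing, and a doorway approach is a different motor state again.

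**Working it through.** **1. How the rule treats each kind of start**

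| Onset of freeze | Label under 2.8.1.5 | What the 5 s before onset hold | Comparator under 2.8.4 |
|---|---|---|---|
| First step after the 1 min stand | Walking-FOG by elimination, as no turn is under way | Standing, reaching back into the baseline minute | Unimpaired walking |
| First forward step after a 360° turn | Not stated; either label is possible | The turn, or standing after it | Unimpaired walking or turning, depending on the label |
| Approach to a doorway or straight walking | Walking-FOG | Regular locomotion | Unimpaired walking (matched) |

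Only the last row satisfies both the like-for-like principle of 2.8.4 and the description of the window in 2.8.2.1.

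**2. The plan's own counts**

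One rotation symbol per door × 10 doors = 10 turns, which agrees with 5 right + 5 left = 10.

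**3. Opportunities per hospital trial**

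- Documented standing starts: 1.
- Implied restarts after turns: up to 10. The text states the stop before the turn; the restart after it is inferred.
- Starts: 1 + 10 = 11, against 10 doors, a ratio of 11/10 = 1.1. If the trial ends at the last turn, 10/10 = 1.0.

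**4. Opportunities over a full session**

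The maximum is 2 blocks × 4 trials = 8 trials. The split between hospital and city is not given, so let h be the number of hospital trials (an assumption). The city scenario has 11 scripted events and no described 360° turns, so each city trial is given one start.

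Starts = 11h + (8 − h) = 10h + 8; doors = 10h.

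| h (assumed) | Starts | Doors | Ratio |
|---|---|---|---|
| 2 | 28 | 20 | 1.4 |
| 4 | 48 | 40 | 1.2 |
| 8 | 88 | 80 | 1.1 |

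Counting only the documented standing starts, the total is at most 8 over 8 trials.

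**5. Form of the bias**

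If a share p of the episodes in the walking-FOG contrast are initiation freezes, and the EEG measure differs between standing or starting and walking by Δ, the contrast moves by p × Δ even with no FOG effect. The document gives neither p nor Δ, so the product has no value that can be computed for this trial.

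**The case against.** The strongest reply has five parts.

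*The label is mostly not stated.* A reader might infer that initiation freezes in general are scored as walking-FOG. The document supports this only for the standing start of a trial. Restarts after a turn are up to 10 of the 11 starts, and they could go either way. This stands. It limits the claim but does not remove the mismatch, since neither label supplies an unimpaired start as comparator.

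*The restarts are implied.* The written standstill comes before the turn, and the first step from it is a turning step, which turning-FOG covers. A participant may step out of the turn without stopping. This also stands. In that case the window holds turning rather than standing, and it is still not regular locomotion.

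*Opportunities are not freezes.* A reader might infer that starts provoke about as many freezes as doorways, or that 11/(11 + 10) = 52% of walking-type triggers are starts. The document gives no freezing rate for any trigger. The 52% covers the hospital scenario alone and accepts every implied restart. With documented starts only it is 1/(1 + 10) = 9%. With an assumed 4 hospital and 4 city trials, and city events counted (4 × 11 = 44), it is 48/(48 + 40 + 44) = 36%. Likewise, setting p at 10% to 50% and Δ at 0.5 to 1 SD gives 0.05 to 0.5 SD, but both ranges are assumptions without a source in the document. Nor are the promised counts by type wrong: under a declared two-class scheme they are coarser, with an unclear boundary at turn exit.

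*RO2 and RO3 focus on doorways.* The Introduction contrasts FOG episodes with unimpaired walking through doorways. That fixes the comparator. It does not restrict the FOG side, which under 2.8.4 takes in all forward-locomotion freezes. The objection therefore carries little weight.

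*The annotation guideline may settle it.* Section 2.8.1.5 follows a published scoring guideline that is not at hand, and it may say how to mark start hesitations or the end of a turn. However, the two-class rule is introduced as a step in addition to that annotation, and 2.8.4 analyses only those two classes.

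**Conclusion.** The point holds in a limited form. The article states an exhaustive two-class rule with two comparators, and that rule does not accommodate a trigger which the article itself names and its tasks include. A freeze at trial start must be coded walking-FOG; a freeze at turn exit has no written rule. Either way, the window before onset does not hold the regular locomotion that the EEG section assumes, and a motor-state difference can enter the RO1 and RO2 contrasts and be carried into RO3.

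On size, the document supports only a count of opportunities: one certain start per trial, and up to 11 starts against 10 doors per hospital trial if every turn is followed by a restart. How many freezes occur at starts, and how far the EEG contrast would move, cannot be derived from it. No sample size or error rate changes. This is a cheap improvement to the scoring and analysis rules and does not invalidate the design.

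**What to change.** In section 2.8.1.5, add a third code, initiation-FOG, for an episode whose onset falls before the first complete forward step after standing or after the end of a 360° turn. Give raters a written rule for when a turn ends, so that turn exits are coded consistently.

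In section 2.8.4, exclude these episodes from both the walking-FOG and the turning-FOG contrast and report their number per participant. If numbers allow, compare them with unimpaired starts from the same trials.

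The cost is one extra annotation code and a sentence or two of analysis text. The videos and synchronized task markers are already planned, so no new data are needed. The downside is somewhat fewer episodes in the main contrasts, by a number that will be known only after annotation.
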